
### Plans to promote participant retention and complete follow-up {18b}

No specific plan was designed to promote participant retention and complete follow-up.

### Data management {19}

The study complies with the European General Data Protection Regulation (GDPR), and data management is under control of Paris-Lumières University local GDPR referent. All parents receive an information note regarding who will have access to data, who is responsible for data management, and regarding the fact that data will be managed in accordance with the GDPR French law. They are also informed that the data provided will be treated confidentially and that in published reports the results will be reported anonymously and at a group level, meaning that it will not be possible to identify any individual or attribute any information to them. Data quality for data collected on paper will be checked by randomly double-checking 20% of data entry. In case of data error, all data will be double-checked.

### Confidentiality {27}

Identity of children participating in the study has been collected from the teachers of the classes involved on paper list by the principal investigators [TV, OC]. All participants have received an anonymous identity code and correspondence between personal identity and code is stored on a file only accessible to the principal investigators [TV, OC].

### Plans for collection, laboratory evaluation, and storage of biological specimens for genetic or molecular analysis in this trial/future use {33}

N/A. This trial will not involve collection and storage of biological specimens for genetic or molecular analysis.

## Statistical methods

### Statistical methods for primary and secondary outcomes {20a}

We will evaluate the effects of the intervention on teachers’ P-WB and on children’s P-WB, self-management, mental health, executive functioning, and school performance. To estimate the effects on all the outcomes listed in the “Outcomes {12}” section, we will run an OLS regression of that outcome on a dummy variable indicating whether the teacher was assigned to the intervention. When necessary, we will add to the model a vector of pre-determined covariates that are unaffected by the treatment such as socio-demographic characteristics or the level of the outcome measured before the start of the intervention. For each estimation, we will cluster the standard errors at the unit of the randomization. In addition to the intention-to-treat (ITT) estimates, we will also compute the treatment-on-the-treated (ToT) estimates using the so-called Wald estimator based on the actual take-up of the intervention according to the measures of fidelity of implementation.

In order to take into account multiple testing issues, we will follow the methodology given in Anderson [5]. First, we will group outcomes into families, and, in each family, we will construct the so-called standardized treatment effect with weights accounting for the variances and covariances of the outcomes, in order to maximize the information captured by the weighted average. Second for each estimation within each family, we will report both the unadjusted *p*-value of the coefficient of the treatment variable, and the *p-*value adjusted for control of the false discovery rate [8].

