**Methods:**

The P-WB promotion intervention is compared to a wait-list control condition in a cluster randomized controlled trial (RCT). Sixty-four pre-Kindergarten classrooms are randomized to the intervention or control group. Primary outcomes measure self-management capacity and core P-WB components: connection, insight, engagement, and positive relationship. Secondary outcomes include measures of mental health, executive functioning, and school performance. Primary and secondary outcomes are assessed through teacher questionnaires, standardized observations of children in school context, and experimental tasks and by collecting results of the national evaluation at first grade. All children-level outcomes are evaluated at pre-intervention, at the end of the intervention, and 1 year later (follow-up analysis), to the exception of school performance which is evaluated at follow-up only. Intention-to-treat analyses, accounting for clustering within classes, will adopt a random effects linear regression model to examine outcomes for the intervention versus control children.

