## Trial design {8}

The trial described in this protocol is a superiority two-armed cluster randomized controlled trial designed to evaluate the value-added of a P-WB promotion curriculum for pre-K children delivered by teachers, compared to teaching as-usual. Sixty-four pre-K classrooms from 50 different schools are randomly allocated to the intervention group or to the control group. In France, preschool classes can either include only students from one school year (here, Pre-K students only, “*moyenne section*” corresponding to 4-year-old children on average) or a mixture of children from Pre-K and kindergarten levels (kindergarten, hereafter K, students, or “*grande section*”, correspond to 5-year-old children on average). In the present sample, 36 classes included only Pre-K students, and 28 classes included a mixture of Pre-K and K levels students. In this context, as we expected potential differential effects according to the type of classroom, we stratified the sample by classroom type in order to compare treatment and control groups within the same type of classrooms. In practice, in the 36 classrooms with only Pre-K students, we randomly assigned 18 classrooms to the treatment group and 18 classrooms to the control group. In the 28 classrooms with a mix of Pre-K and K students, we assigned 14 classrooms to the treatment group and 14 classrooms to the control group. Overall, the treatment group and the control group are both composed of 32 classrooms.

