### Eligibility criteria {10}

*Inclusion criteria*: children at pre-K level (*moyenne section*) attending public schools.

*Exclusion criteria*: parent refusal for the child to participate in the study or consent withdrawal during the study.

*Specific exclusion criteria for collection of experimental data and observations*: (1) children showing comprehension difficulties in French language; (2) children with high difficulties in expressive French language or children who do not speak French; (3) children with suspicion of neurodevelopmental disorders (notably intellectual disability or Autistic Spectrum Disorder); (4) children with severe behavior problems (e.g., high aggression/tantrum level) whose teachers judged that taking part in the experimental part of the protocol would not be possible. These criteria were implemented to ensure that experimental data collection would be feasible with the selected children. Teachers were asked to exclude children based on this list of criteria.

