### Sample size {14}

A previous meta-analysis of SEL interventions in preschool children found effects in the medium range (mean of 0.35 standard deviations) for socio-emotional outcomes [56] while intra-cluster coefficient (hereafter ICC) for socio-emotional measures are typically between 0.02 and 0.2 for teacher-reported outcomes [23, 32, 38] and inferior to 0.1 for behavioral tasks such as executive functioning tasks [38, 40].

We performed power calculations in order to estimate the number of classrooms required to observe a minimum detectable effect size (MDES) of 0.35 standard deviations, as expected from the meta-analyses of Murano et al. [56]. We followed Bloom [12] to perform rigorous clustered-design power calculations and took into account the various parameters that can affect the sample size required to detect a specific MDES. In particular, we took into account various levels of the ICC, attrition rate, and augmented power coming from control variables. Overall, for a total number of 10 observed students per classroom, we needed to recruit at least 55 classrooms to observe an MDES of 0.35 standard deviations.

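### Baseline adjustment is optional, the randomisation stratum has no term in the stated model, and the abstract and section {20a} name different estimators; the power cost is confined to high ICCs

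*Protocol article*

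**What the plan says.** Four places in the protocol article bear on the primary model.

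- **Statistical methods {20a}.** Each outcome is regressed by OLS on a dummy for the teacher's assignment, with standard errors clustered on the randomised unit. On covariates: "When necessary, we will add to the model a vector of pre-determined covariates that are unaffected by the treatment". Socio-demographic variables and the pre-intervention outcome are given as examples. No criterion for necessity, no fixed list and no term for classroom type are stated.
- **Trial design {8}.** Of the 64 classes, 36 are Pre-K only and 28 are mixed, allocated 1:1 within each type. The reason given is that "we stratified the sample by classroom type in order to compare treatment and control groups within the same type of classrooms".
- **Sample size {14}.** On the inputs: "we took into account various levels of the ICC, attrition rate, and augmented power coming from control variables". The result, with ten children observed in each class, is put this way: "we needed to recruit at least 55 classrooms to observe an MDES of 0.35 standard deviations". No single ICC, R2, attrition rate, alpha or power is given.
- **Abstract, Methods.** The intention-to-treat analyses "will adopt a random effects linear regression model to examine outcomes for the intervention versus control children".

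**The concern.** The baseline value of every child outcome except school performance is collected, and classroom type is known for all 64 classes. The model nevertheless leaves the first to later judgement and does not mention the second. With baseline in or out, class type in or out, and OLS or random effects, the text admits 2 × 2 × 2 = 8 versions of each primary estimate before any socio-demographic covariate is considered. There are 15 primary variables.

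Two further consequences follow. The sample size took credit for a precision gain that the analysis does not commit to. And a design balanced within class type, if analysed without that factor, gives standard errors that are too wide whenever the types differ on the outcome.

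**Working it through.** **Inputs from the protocol.** Target 0.35 SD; at least 55 classes; 10 observed children per class; 64 classes randomised 32:32. On ICCs: "intra-cluster coefficient (hereafter ICC) for socio-emotional measures are typically between 0.02 and 0.2 for teacher-reported outcomes", and below 0.1 for behavioural tasks. Questionnaires cover the 12 selected children, 2 on the waiting list and up to 2 with severe behaviour problems, so 14 to 16 per class where the class is large enough (Recruitment {15}).

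**Assumptions.** Two-sided 5%, 80% power, equal arms, no attrition, and the same R2 at class and child level.

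**Formula.** MDES = M × sqrt{4(1 − R2)[ICC/J + (1 − ICC)/(J·n)]}, with M = t(0.975, J−2) + t(0.80, J−2). M is about 2.854 for J = 55 and 2.847 for J = 64.

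**1. The plan's own figure.** The 55 cannot be reproduced uniquely because its inputs are not stated. At 80% power several sets come close:
- ICC 0.12 with R2 = 0 gives 56 classes (54 by the normal approximation).
- ICC 0.15 with R2 = 0.10 gives 57 (55).
- ICC 0.20 with R2 = 0.25 gives 56 (54).

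At 90% power, ICC 0.10 with R2 = 0.20 gives 55. The reader cannot tell how much the figure leans on covariates.

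**2. Unadjusted MDES.** Example for J = 64, n = 10, ICC 0.20: 2.847 × sqrt{4(0.20/64 + 0.80/640)} = 2.847 × 0.1323 = 0.377.

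| Classes × children | ICC | MDES | Power for 0.35 SD |
|---|---|---|---|
| 55 × 10 | 0.02 | 0.264 | 96% |
| 55 × 10 | 0.10 | 0.336 | 83% |
| 55 × 10 | 0.15 | 0.373 | 75% |
| 55 × 10 | 0.20 | 0.407 | 67% |
| 64 × 10 | 0.10 | 0.310 | 89% |
| 64 × 10 | 0.15 | 0.345 | 81% |
| 64 × 10 | 0.20 | 0.377 | 74% |
| 64 × 14 | 0.20 | 0.361 | – |
| 64 × 16 | 0.20 | 0.356 | – |

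**3. Largest ICC at which 0.35 SD is met unadjusted.** Solve ICC + (1 − ICC)/n = (0.35/M)² × J/4. With n = 10:
- J = 64: the right side is 0.2419, so ICC = (0.2419 − 0.1)/0.9 = 0.158.
- J = 55: the right side is 0.2068, so ICC = 0.119.

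With J = 64, the limit is 0.184 for n = 14 and 0.191 for n = 16. If only 8 children per class are analysed, the limits are about 0.134 (64 classes) and 0.093 (55 classes).

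**4. What adjustment has to deliver at ICC 0.20.** The R2 needed is 1 − (0.35/MDES)²: 0.26 for 55 × 10, 0.14 for 64 × 10, 0.06 for 64 × 14 and 0.03 for 64 × 16. With an assumed R2 of 0.30 and n = 10, the MDES falls to 0.315 (64 classes, power 88%) or 0.341 (55 classes, power 82%).

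**5. Omitted stratum.** Take ICC 0.10 and n = 10. The variance of a class mean within type is 0.10 + 0.90/10 = 0.19. An assumed 0.4 SD difference between types adds (36/64)(28/64)(0.4²) = 0.039 to the variance that the unstratified model sees. The standard error is then inflated by sqrt(0.229/0.19) = 1.10. A simulation of 64 classes (6,000 runs) agreed: type I error was 3.2% instead of 5.0%, and power 84% instead of 88%. With no difference between types nothing is lost.

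**The case against.** The strongest reply has five parts.

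- **Covariates are evidently intended.** Section {20c} says how missing control variables are handled in the final treatment-effect regressions, and the examples in {20a} do not exclude classroom type. This stands: the bare model is not firmly the plan. What stays open is the rule.
- **Such detail belongs in an analysis plan.** A full covariate list may well. But {20a} states a rule, and the rule is discretionary. The article gives numerical go/no-go criteria for one subgroup analysis in {20b}, and the trial status section ties the start of analysis to publication of this text. The clash between abstract and {20a} needs no further document to be seen.
- **Analysts are blinded.** This lowers the risk of choosing a model by its result but does not remove it. The principal investigator who carries out the analysis is also named as receiving the intervention session recordings ({11c}) and as collecting the commitment measure, which only intervention teachers answer ({18a}).
- **Omitting the stratum is harmless to validity.** Correct: there is no bias, and the test is conservative. The cost is precision, and only if class types differ.
- **Power is mostly adequate.** Also correct. A reader might infer that without covariates 0.35 SD is missed over the protocol's whole ICC range. The figures do not support that: task outcomes with ICC below 0.1 reach it with 55 or 64 classes of 10.

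A reader might also infer that children were listed after classes were allocated, so that baseline differences are not chance alone. The eligibility section says "Teachers were asked to exclude children based on this list of criteria" but gives no timing, and no randomisation date appears anywhere. The parent letter's conditional mention of intervention benefits makes this plausible, not established.

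**Conclusion.** The point holds as a fault of pre-specification and of matching analysis to design. Adjustment for a baseline that is already collected is optional without a criterion, the stratum has no named term, and two estimators are announced that can differ in weighting and standard errors.

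The power consequence is small and local. With the 64 classes randomised, an unadjusted analysis falls short of 0.35 SD only above an ICC of about 0.16 with 10 children, or about 0.18 to 0.19 with 14 to 16. At ICC 0.20 the shortfall is about 0.03 SD with 10 children and about 0.01 SD with 14 to 16. The protocol cites ICCs that high only for teacher-rated outcomes, which are 7 of the 15 primary variables (five PKBS subscales and two STRS scores). Attrition would widen the gap.

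These sizes rest on the assumed 80% power, two-sided 5% and equal class sizes. The stratum figures rest on an assumed 0.4 SD difference between class types.

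**What to change.** - In {20a}, replace the discretionary clause by a fixed rule: every T1 and T3 child outcome is regressed on treatment, its own baseline value and a classroom-type dummy, with standard errors clustered on the randomised classroom. School performance has no baseline of its own and includes at least the classroom-type dummy.
- Report the unadjusted model as a sensitivity analysis, particularly for teacher-rated outcomes, whose baselines may have been given with allocation known.
- Make the abstract name the same estimator as {20a}.
- In {14}, state the ICC, R2, attrition, alpha and power under which 55 classes give 0.35 SD.

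The cost is wording only. Baselines and classroom type are already collected, and {20c} already covers missing control values. The change should be made before anyone analyses outcomes by arm.

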### Interim analyses {21b}

N/A. No interim analyses are planned.

### Methods for additional analyses (e.g., subgroup analyses) {20b}

We will estimate the effects of the intervention on the children’s and teachers’ outcomes listed in the “Outcomes {12}” section based on the following characteristics:Girls (for the children)Level of experience of the teachers (according to the median)Age of the teachers (according to the median)Initial levels of EF, connection, and problem behaviors of the childrenMulti-level classesTeachers predicted to have a high degree of commitment with the intervention by a machine learning model

According to the data collection plan detailed in this paper, we will ask questions about treatment-group teachers’ commitment with the intervention (see Plans for assessment and collection of outcomes {18a} section) and will average teachers’ answers into a standardized score of their commitment with the intervention. Then, we will run a Lasso regression [7] of that score on all the socio-demographic variables and the outcomes listed in the “Outcomes {12}” section measured at baseline, on the square of those variables, and on the products of all the pairs of variables. We will then use the Lasso regression to predict the commitment score of every teacher included in the experiment, hence including teachers in the control group. Finally, teachers predicted to have a high degree of commitment with the intervention will be those with a predicted score above the median. To compute predicted commitment with the intervention for treatment group teachers, we will use a leave-one-out method, as suggested by Abadie et al. [1]. It may however be the case that we are not able to predict the teachers’ commitment score very well, in which case, undertaking that third subgroup analysis would not be informative. If the Lasso regression does not select any variable, or if the R2 of the OLS regression of the commitment score on all the variables selected by the Lasso regression is below 0.1, we will not conduct that subgroup analysis.

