## Objectives {7}

This trial evaluates the impact of an incremental P-WB curriculum delivered in French preschools, (1) after 24 weeks of program exposure in children 4 to 5 years old (during *moyenne section* in France: US Pre-K equivalent) and (2) 1 year later (end of *grande section:* US kindergarten equivalent; follow-up analysis).

Our primary objective is to assess the effects of the curriculum on P-WB-related measures of *Connection, Insight*, *Engagement*, *Positive Relationships*, and *Self-management*. Our secondary objective is to document the effects of the curriculum on measures of mental health, executive functioning, and school performance [51]. We hypothesize that the intervention will lead to more favorable outcomes on P-WB, mental health, and executive functioning measures after 24 weeks of program exposure, that these effects will be maintained 1 year later, and that school performance at the national evaluation 2 years later will be superior in children who received the intervention compared to the control group.

We also investigate heterogeneous effects according to teacher-level and children-level characteristics. In terms of teacher-level characteristics, we first investigate heterogeneity according to teacher P-WB since higher levels of P-WB are associated with higher impacts in various interventional settings [25, 47, 52, 75]. Second, we will use a machine-learning model to assess potential heterogeneous effects of the curriculum according to the teachers’ level of commitment in implementing the intervention (see the “Methods for additional analyses (e.g., subgroup analyses) {20b}” section for additional details). Higher levels of fidelity of implementation are associated with higher gains in children’s P-WB, mental health, and executive functioning [40, 56]. In terms of children-level characteristics, we investigate heterogeneity according to the initial levels of EF, *connection*, and problem behaviors. Lower pre-intervention levels of EF and *connection* are associated with higher gains in EF [38, 73] and *connection* [73] respectively. Similarly, higher pre-intervention levels of problem behaviors are associated with higher reductions in post-intervention problem behaviors [38].

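### Predicted-commitment subgroup: ranking leave-one-out predictions on one median can sort intervention teachers against their own commitment if the Lasso penalty is re-tuned in each fit

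*Protocol article*

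**What the plan says.** The Objectives {7} name teacher commitment as a source of heterogeneity: "we will use a machine-learning model to assess potential heterogeneous effects of the curriculum". Section {20b} gives the procedure.

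- Commitment is measured in the intervention arm only ("we will ask questions about treatment-group teachers"). By Trial design {8}, "the treatment group and the control group are both composed of 32 classrooms", so at most 32 scores train the model.
- The Lasso uses baseline socio-demographic variables and outcomes and expands them "on the square of those variables, and on the products of all the pairs of variables".
- The investigators will "use the Lasso regression to predict the commitment score of every teacher included in the experiment, hence including teachers in the control group".
- For the intervention arm the scoring differs: "To compute predicted commitment with the intervention for treatment group teachers, we will use a leave-one-out method".
- The split is then that "teachers predicted to have a high degree of commitment with the intervention will be those with a predicted score above the median".

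The analysis is dropped if the Lasso selects nothing, or if an OLS regression of commitment on the selected variables has an R2 under 0.1. The section does not say how the penalty is chosen, whether tuning is repeated in each leave-one-out fit, or whether the median is pooled or taken within arm.

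**The concern.** Leave-one-out predictions come from 32 separate fits, and each fit is shifted by the teacher it omits. Removing a committed teacher lowers the mean of the remaining 31, and removing an uncommitted one raises it. When prediction is weak, this shift can outweigh the real signal and carry the teacher to the wrong side of the median. Control predictions all come from one fit and have no such dependence.

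'High' and 'low' would then mean different things in the two arms, and the comparison inside each subgroup would not be like with like. The protocol expects better implementation to bring larger gains. The distortion works against that direction, so a real gradient could be hidden or reported with its sign reversed.

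**Working it through.** **Inputs.** 32 teachers per arm: 18 + 14 = 32 (Trial design {8}). The outcome tables list 15 primary variables, 2 SDQ scores and 3 executive-function scores, so 20 base variables. Terms: 20 + 20 squares + (20 x 19)/2 = 190 products = 230. Socio-demographic variables would add more.

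**Algebra.** A leave-one-out fit that selects no variable predicts the mean of the others:

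prediction = (32 x mean - own score) / 31.

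This falls by 1/31 for each unit of own score. With the mean at 0, a teacher at +1 SD is predicted at -1/31 = -0.032 SD and a teacher at -1 SD at +0.032 SD. Among such fits the ranking is exactly reversed.

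**How often fits are empty.** With the penalty re-tuned by cross-validation in each fit, simulated shares are about 35%, 29% and 17% at true R2 of 0, 0.1 and 0.3. Out of 32 that is about 11, 9 and 5 teachers (0.35 x 32 = 11.2; 0.29 x 32 = 9.3; 0.17 x 32 = 5.4).

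**How the arms are sorted.** Simulation with 230 terms, 5-fold cross-validation, both stop conditions applied, and about 1,150 to 1,280 retained trials per setting. Entries are actual commitment, 'high' minus 'low', in SD.

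| True R2 | Intervention, re-tuned | Control | Intervention, one penalty held fixed | Control |
|---|---|---|---|---|
| 0 | -0.58 | 0.00 | -0.01 | -0.01 |
| 0.1 | -0.40 | +0.12 | +0.13 | +0.12 |
| 0.3 | +0.05 | +0.46 | +0.45 | +0.46 |

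At R2 up to about 0.1 with re-tuning, 59 to 64% of the intervention 'high' group are below median commitment. A separate simulation found much the same whether the median was pooled or taken within arm.

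**Spread between implementations.** Other re-tuned runs gave -0.56 and -0.84 SD at R2 0, -0.43 and -0.72 at 0.1, and +0.11 and -0.19 at 0.3. Results with a held penalty agree less well. Two further sets of runs found no reversal, but one still gave -0.52, -0.38 and +0.14 SD at R2 0, 0.1 and 0.3.

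**The stop rule.** Its R2 comes from the same teachers on whom the variables were selected. With no true signal, the analysis still went ahead in 38% of trials (43 to 45% in a second simulation with cross-validated tuning).

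**Effect scale.** Assume the treatment effect rises by 0.2 SD per SD of commitment, with 24 base variables (324 terms), an ICC of 0.1, 10 children per class and re-tuning. The comparator is the same rule trained on an independent sample of 32.

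| True R2 | Mean high-minus-low effect difference | Comparator |
|---|---|---|
| 0 | -0.09 to -0.10 | -0.03 |
| 0.1 | -0.05 to -0.06 | +0.04 |
| 0.3 | about +0.01 | +0.08 |
| 0.5 | about +0.11 | +0.15 |

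Now assume instead a uniform effect, an ICC of 0.15 and a correlation of 0.5 between commitment and the class component. The estimated difference was -0.12, -0.10 and -0.09 SD at R2 0, 0.1 and 0.3, where the truth is 0. If commitment is unrelated to outcome, the mean difference is about 0.

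**The case against.** A reader might infer that using leave-one-out in one arm and a full model in the other is itself the error, and that the result will usually have the wrong sign. The document does not support that.

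- Control teachers did not train the model, so their full-model score is already out of sample. Leave-one-out is a reasonable way to put intervention teachers on the same footing. Scoring them in-sample would be worse: the spurious difference was +0.22 to +0.24 SD at R2 0. The fault lies in ranking separately re-tuned, sometimes empty, fits on one cut.
- The tuning rule is not stated, and an article may leave it to an analysis plan or code. The lack of that detail is not the point here. With one cross-validated penalty held fixed, most simulations sort the arms alike. A very conservative penalty reverses the ranking strongly, but the stop rule then cancels nearly all such analyses (run in about 0.3% of trials at R2 0 and 4% at 0.3).
- Wrong signs are partly noise. With re-tuning, the estimate was negative in 56 to 63% of trials at R2 up to 0.1, against 42 to 52% with independent training.

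These objections make the claim conditional. They do not remove it: re-tuning within each fit is an ordinary reading of the text, and the stop rule does not catch the problem.

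**Conclusion.** The concern holds conditionally. If the penalty is re-tuned in each leave-one-out fit and true predictive R2 is about 0.1 or less, the intervention split tends to run against actual commitment (about -0.4 to -0.6 SD, against 0 to +0.1 in controls). At R2 0.3 the intervention arm is hardly sorted (+0.05 against +0.46), and by 0.5 the problem has largely faded. Bias in the effect contrast also requires commitment to be related to outcome. Its size, around a tenth of an SD in the settings tried, rests on the assumed predictors, slope, correlation and ICC.

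The problem is absent in most, though not all, simulations with one cross-validated penalty tuned once and held. Primary and secondary intention-to-treat estimates are not affected. Severity is minor: one subgroup analysis that is itself subject to a stop rule.

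**What to change.** In {20b}, replace the leave-one-out scoring with repeated split-sample scoring. Fit the Lasso on a random half of the intervention teachers, and score the other half and all controls with that one model. Split at that model's median, drop splits in which no variable is selected, and average over many splits. In simulation this nearly balanced the arms: intervention against control was +0.08 and 0.00 at R2 0, +0.11 and +0.07 at 0.1, and +0.27 and +0.26 at 0.3.

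If leave-one-out is kept, tune the penalty once on all 32 intervention teachers and hold it fixed in every fit. Because one set of runs still showed a reversal under a held penalty, check the chosen code by simulation first.

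Do not cut each intervention teacher at the median of the control predictions from that teacher's own leave-one-out model. At R2 0 that over-corrects: +0.17 SD with re-tuning and +0.48 SD with a held penalty, against 0 in controls.

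The cost is a short change to {20b} and slightly longer code, with no new data. Each split-sample model trains on 16 teachers, so the commitment contrast is weaker.
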